**Figure 2 fig2:**
[figure not shown]
Safe landing techniques.

To minimize the risk of injury, participants will practice the safe landing techniques on 12-inch thick gymnastics crash landing mats. The instructor will exemplify the technique before the participants. Each technique will be introduced gradually to protect the participants from falling directly at the beginning. In addition, two professionals will assist the participants’ movements to ensure their safety throughout the session. Participants will be encouraged to lower their center of gravity and increase the area of their body’s contact with the mats to decrease impact load. To help to protect the vital organs from damage, they must exhale to contract the muscles and constrict the rib cage on impact.

Participants will keep repeating the safe landing techniques to establish the conditioning reflex of instinctively and quickly assuming the movements to protect themselves, exha-le, relax, and allow the impact to spread through the body without injury.

To finalize, participants will perform five minutes of relaxation with active slow amplitude movements with music, stretching, and breathing exercises, followed by a brief group discussion to gather participant feedback on each exercise to guide future sessions.

The structure of the Safe landing training sessions is described in Table 2.

**Table 2 tab2:** Structure of the safe landing training sessions.

Phase 1: Warm-up (10 min)	Warm-up exercises to prepare participants for safe landing training. Mobility and flexibility exercises
Phase 2: Improvisation (10 min)	Participants have the freedom to move according to specific instructions. Encouraging participants to explore their movements and expand their physical capabilities.
Phase 3: Safe landing practice (20 min)	Guided practice of safe landing techniques with instructor supervision Participants practicing controlled landings and loss of balance. Participants practicing safe landing techniques independently. Instructor providing feedback and corrections as needed.
Phase 4: Cool-Down and Conclusion (5 min)	Cool-down exercises to relax muscles after safe landing practice. Summary of the key points covered in the safe landing training.

### Data collection

2.5.

Researchers defined the feasibility of trial design and procedures by six key domains for a subsequent registered randomized controlled trial. These key domains will be our primary outcomes and include:

Recruitment strategy and rates (candidates screened, eligible, approached, consented, and excluded after screening).Enrollment (number of participants that attended the program).Retention (percentage of enrolled participants who completed final program assessments).Acceptability (assessed with an *ad hoc* survey and semi-structured exit interviews). The exit survey will consist of Likert scale questions to evaluate the participants’ satisfaction. The interviews aim to gain insight into participants’ perspectives on the intervention’s feasibility, acceptability, and usefulness and identify barriers and facilitators that may influence people with PD to participate in the program.Reasons for decline/withdrawal (the researchers will keep a record of reasons for decline/withdrawal).Adverse events (number of events involving injury).

A qualified research team member will collect secondary outcomes to identify an appropriate outcome and estimate parameters for a sample size calculation for a randomized controlled trial. These assessments will be performed in the week before (T0) and after completing the training program (T1) using the following instruments:

FOF (Short FES-I). The Short FES-I is a self-report questionnaire used to assess an individual’s level of concern or FOF during various activities of daily living. The ratings are often done on a scale, typically ranging from 1 (not at all concerned) to 4 (extremely concerned). This scale had good test–retest reliability (*r* = 0.987) and good internal consistency (*α* = 0.958) (33);Clinical impairments (The Movement Disorder Society Unified Parkinson Disease Rating Scale - MDS-UPDRS) (44). The MDS-UPDRS is a comprehensive clinical assessment tool to evaluate non-motor and motor experiences of daily living and motor complications. It includes a motor evaluation and characterizes the extent and burden of disease. This scale had a test–retest reliability of 0.92 and internal consistency of 0.96 (45);Frequency and severity of falls (falls weekly registry). The registry collects data on falls, including when and where they occurred, the circumstances surrounding the falls, the individuals involved, and any resulting injuries (46);Gait (Timed Up Go - TUG). The Timed Up and Go Test is a reliable assessment tool for evaluating an individual’s mobility and functional balance, as it necessitates the ability to transition, walk, and change direction (46). Concerning the test–retest reliability of TUG, the intra-class correlation coefficient (95% CI) for the total score was equal to 0.96 and presented excellent internal consistency (*α* = 0.98) (47). Participants will begin in a seated position with their backs supported and are required to stand, walk 3 meters in a straight line, pivot, return to the chair, and sit down, mirroring the initial position. The test score is determined based on the participants’ time to complete the task. Completion within 10 s indicates normal mobility, while a duration of 11–20 s falls within the normal range for frail or partially independent adults with disabilities. A completion time exceeding 20 s is typically observed in individuals with a significant mobility impairment (46).Physical capacity (6 min walking distance test - 6MWD). The 6MWT evaluates a person’s exercise tolerance, functional capacity, and endurance. Participants are instructed to walk back and forth in a hallway as far as they can within 6 min. They can walk at their own pace, and they are allowed to slow down, stop, or rest during the test if needed (46). This test presented excellent test–retest reliability (intra-class correlation coefficient = 0.95–0.96) (48).

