### Intervention

2.4.

The intervention consists of an 8-week program with 90-min group sessions held twice a week. The program combines group CBT with training in safe landing strategies, thus ensuring each component receives dedicated 45-min sessions (35, 37, 38). This intervention will supplement the usual care.

The intervention will be delivered by a rehabilitation nurse with PhDs in Nursing Sciences and Psychology, trained in Cognitive behavioral therapy, and experienced in motor and cognitive exercise programs. Following European Parkinson’s guidelines (35), we will consider eight people with PD as the optimum number of participants per group.

Assistance to the instructor will be provided by two nurses that are receiving their master’s training in rehabilitation nursing. In addition, the students will receive 8 h of CBT training conducted by a cognitive-behavioral therapist.

To keep the program challenging and engaging, the instructor will gradually raise the complexity of the exercise session accordingly to the participants’ willingness and improved condition. The instructor will use the Borg Effort Perception Scale to assess the participants’ perceived effort through sessions (39). Participants can achieve an intensity rating between 14 (Somewhat Hard) and 17 (Very Hard) on a 20-point Borg scale, indicating a range from somewhat challenging to very hard perceived exertion during exercise (40).

The CBT will be based on the FOF management model (41) that illustrates how community-dwelling older adults think, feel, and act when facing FOF. According to this model, the FOF arises when the person believes falling is an inevitable part of aging. These misconceptions may lead older adults to withdraw from social activities instead of focusing on strategies to manage the problem. The FOF model indicates that older adults may embrace different strategies: display psychosomatic symptoms, adopt an attitude of risk prevention, pay attention to environmental safety, and modify their own’s behavior. The FOF will be relieved when the person is satisfied with the outcomes (41).

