Although training safe landing techniques can be well accepted and enjoyable workout activity (50, 51), we acknowledge that it can also be intimidating for some people with FOF. However, the safety measures introduced by researchers can potentially mitigate this effect. In addition, the program has the potential to promote social interaction, as it will be performed in a group format. Thus, it is expected to develop a sense of camaraderie between participants (52, 53) and accomplishment (54), contributing to the intervention’s satisfaction (52, 54). Given all these aspects, combining CBT and safe landing strategies can be an especially well-adapted and attractive way of optimizing care for people with PD.

Like in previous research that employs a safe landing intervention, we expect the level of risks associated with being low (50, 51). However, the potential risks should be foreseen and addressed to ensure participants’ safety. Therefore, in addition to the protective gear and mattress, the instructor can adapt the exercise program to each participant’s skills and abilities to keep it challenging and engaging.

This study has limitations. First, as we intend to establish the program’s feasibility, the study procedures do not include a control group, which will prevent comparing the program’s effects to additional treatment. Second, when evaluating the program’s feasibility, we recognize the possibility of bias due to social desirability. As such, participants’ reports might diverge from their real perceptions and feelings. To minimize the effect of this bias during the qualitative assessment, we will implement practices recommended by Bergen and Labonté (55). Therefore, all study details will be explained clearly to participants, including confidentiality and anonymity procedures, how the data will be used, and the dissemination of results. We will conduct the interviews in a private location and not within earshot of others. The interviewer will resort to different methods to establish rapport with participants (e.g., humor, self-disclosure, making displays of respect).

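### The primary adverse event domain counts only events involving injury, so non-injury medical events and acute distress in participants who continue fall outside the safety outcome

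*Protocol article*

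**What the plan says.** Section 2.5 (Data collection) lists six feasibility domains and gives them primary status: "These key domains will be our primary outcomes and include". One of them is "Adverse events (number of events involving injury". The Abstract names the same domain simply as adverse events, with no qualifier, and no other section gives a wider definition.

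Three other places describe what participants are exposed to:

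- Section 2.4 (Intervention), on dose: "The intervention consists of an 8-week program with 90-min group sessions held twice a week".
- Section 2.4, on effort: "Participants can achieve an intensity rating between 14 (Somewhat Hard) and 17 (Very Hard) on a 20-point Borg scale".
- Table 2, within the 20-minute landing phase: "Participants practicing controlled landings and loss of balance".

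Section 3 (Discussion) says of the landing training: "we acknowledge that it can also be intimidating for some people with FOF". It also expects risk to be low, and it says the study's results will settle whether a full trial is feasible.

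**The concern.** The definition does not match the harms that the article's own description makes foreseeable. Hard exertion in people at Hoehn and Yahr stages II to IV can produce fainting, dizziness, chest symptoms or pain without any injury. Practising loss of balance can cause acute distress in people selected for concern about falling (Short FES-I above 9). None of these is an event involving injury.

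What is at stake is how the safety domain will be read. A small or zero count reported under the label adverse events will be taken as a statement about harm in general, when it is a statement about injury alone. It would then support the move to a randomized trial, and the design of safety monitoring in that trial, without showing whether non-injury events occurred.

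**Working it through.** **1. The plan's own figure.** The article gives no adverse event rate. Its only sample size (section 2.3) fixes how many people are observed. Inputs: dz = 0.8, two-sided alpha 0.05, power 0.80, dropout 25%.

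- Paired t-test, n = 15: noncentrality 0.8 × √15 = 3.10 on 14 degrees of freedom, power 0.821.
- Wilcoxon signed-rank with normal-parent efficiency 3/π, n = 15: power 0.801.
- Dropout: 15 / (1 − 0.25) = 20.

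Both 15 and 20 reproduce. The point disputes no figure in the plan.

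**2. Where each foreseeable event would be recorded.**

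| Event | In the adverse event count? | Other route in the article |
|---|---|---|
| Injury in a session | Yes | Falls registry, if from a fall |
| Fall without injury | No | Weekly falls registry (secondary outcome) |
| Distress leading to withdrawal | No | Record of withdrawal reasons (primary domain) |
| Change in fear from T0 to T1 | No | Short FES-I, tested as a paired group difference |
| Feeling intimidated | No | Exit survey, exit interviews, session feedback |
| Faint, dizziness, chest symptoms or pain without injury, participant continues | No | No named count |
| Acute distress in a session, participant continues | No | No named count; may be mentioned in feedback or interview |

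The last two rows are the gap.

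**3. How an undercount would behave (assumed inputs).** Let p be the share of 20 participants with any adverse event, and s the share of those affected who have no injury. Treat participants as independent.

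- Expected number affected = 20p; expected number counted = 20p(1 − s).
- Chance of zero under a full definition = (1 − p)^20; under the injury definition = (1 − p(1 − s))^20.

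| p | s | Affected | Counted | Chance of zero, all events | Chance of zero, injury only |
|---|---|---|---|---|---|
| 0.10 | 0.25 | 2.0 | 1.5 | 0.122 | 0.210 |
| 0.10 | 0.50 | 2.0 | 1.0 | 0.122 | 0.358 |
| 0.10 | 0.75 | 2.0 | 0.5 | 0.122 | 0.603 |
| 0.20 | 0.25 | 4.0 | 3.0 | 0.012 | 0.039 |
| 0.20 | 0.50 | 4.0 | 2.0 | 0.012 | 0.122 |
| 0.20 | 0.75 | 4.0 | 1.0 | 0.012 | 0.358 |

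If s = 0 there is no undercount. The table shows direction and sensitivity; it does not estimate what will happen in this study.

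**4. Sample-size context only.** With no participant affected, the exact two-sided 95% upper limit is 1 − 0.025^(1/n): 16.8% for n = 20 and 21.8% for n = 15. These limits hold under any definition and do not measure the defect.

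**The case against.** The strongest reply is that much non-injury harm is recorded somewhere. The weekly registry takes all falls, with injury as one field and not a condition of entry, and nothing excludes falls in class. For withdrawals, "the researchers will keep a record of reasons for decline/withdrawal", which is itself a primary domain feeding the same decision. Fear of falling is measured directly at T0 and T1, and intimidation can emerge in the survey and interviews. All of this stands. A reader might infer that non-injury harms would go wholly unrecorded; the article does not support that.

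These routes still do not fill the gap. Withdrawal reasons cover only those who leave. Short FES-I is analysed as a group difference, so deterioration in a few can be hidden by improvement in others, and people who stop may have no T1 score. Interviews and session feedback do not produce a count of harms.

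A reader might also infer that the study will overstate safety. That would require non-injury events to occur and the other domains to be ignored. The article gives no event rate and no adverse event threshold for proceeding, so the inference goes too far.

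Finally, grading, relatedness, denominators and intervals are details that an article commonly leaves to the full protocol or analysis plan, and their absence is not a fault here. The injury restriction is different: the article states it as the definition of a primary outcome.

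**Conclusion.** The point holds as a defect in a stated definition. The adverse event domain is an injury count under a broader name. Two kinds of event, non-injury medical events and acute distress in participants who continue, are left out of it and have no other named count. Other non-injury problems can surface in neighbouring domains, but not as adverse events.

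The size of any undercount is unknown. Over the assumed range in the working, the chance of reporting zero affected participants out of 20 rises from 0.122 to between 0.210 and 0.603 when 10% are affected, and from 0.012 to between 0.039 and 0.358 when 20% are. These figures rest on the assumed p and s, on independence between participants and on all 20 being observed. The conclusion about the definition needs none of these assumptions. The change should be made before recruitment, since events that were not logged are hard to recover afterwards.

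**What to change.** In section 2.5, redefine the domain as any untoward medical or psychological event from the first session to T1, whether or not injury results, and keep injury as a subcategory so that the planned count is still available. Report the number of participants with at least one event among all who attended at least one session, including those who stopped. State that falls in class and withdrawals because of an event are carried into this count from the registry and the withdrawal record. Set out in the session log what qualifies as a psychological event, so that it is not confused with ordinary change in Short FES-I. If the full protocol already uses a wider definition, the article and that document need to be brought into line.

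The cost is a somewhat longer session log and some staff time to judge psychological events. More events will be listed, so the safety profile may look less favourable. The intervention and the sample size do not change.

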### Sampling and recruitment

2.3.

The study population consists of people with PD recruited from the Parkinson Patients Association and the outpatient neurology units from two hospital centers in Lisbon and Tagus Valley. The sampling method selection will be non-probabilistic by convenience. All eligible candidates will be invited to join the program.

Participants will be included if they fulfill the inclusion criteria:

Diagnosis of idiopathic PD (Movement Disorder Society PD criteria) (31);Hoehn and Yahr stages II–IV (32);Age above 18;Moderate concern of falling with the Short Falls Efficacy Scale International (Short FES-I) >9 (33);A Montreal Cognitive Assessment (MoCA) score > 25 (Normal cognition) (34);Able to tolerate a minimum of 45 min of exercise (Following recommendations form PD guidelines) (35);Able to communicate with the investigator, to understand and comply with the study procedures;Willing and able to provide written informed consent to participate and understand the right to withdraw their consent at any time without prejudice to future medical care.

Participants will be excluded if they have any of the following:

A MDS-UDPRS Part III item 3.12 score > 3 (Severe postural instability: very unstable, tends to lose balance spontaneously or with just a gentle pull on the shoulders);Severe cognitive difficulties and significant active psychiatric problems that aggravate when exercising;Severe hearing or visual impairment;Missed two consecutive sessions.

Our study aims to recruit 20 participants in total. This sample size was calculated using G*Power (36), taking into account a large effect size (dz = 0.8), an alpha level (α) of 0.05, and a statistical power (1-β) of 0.8. These calculations were performed for both the two-tailed matched pairs t-test and the two-tailed matched pairs Wilcoxon signed-rank test, which will be employed in the quantitative data analysis. Further details about these analyses are provided in the data analysis section below. Both tests indicated a required sample size of 15 participants. To account for a possible dropout rate of 25%, we increased the sample size to 20 participants.

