
### Data analysis

2.6.

Quantitative method: the sample will be characterized using descriptive statistics, including measures such as count, mean, standard deviation, median, minimum, maximum, and range. Differences between the scores obtained from initial and final assessments for Short Falls Efficacy Scale-International (Short FES-I), Movement Disorder Society Unified Parkinson’s Disease Rating Scale (MDS-UPDRS), Timed Up Go (TUG), 6 Minutes Walking Distance (6MWD), and frequency and severity of falls will be evaluated using inferential statistics. Specifically, the parametric two-tailed paired samples t-test will be employed if the normality assumptions are met. Alternatively, the non-parametric two-tailed matched pairs Wilcoxon signed-rank test will be utilized in case of normality deviations. The statistical analysis will be conducted using the R statistical computing software.

Qualitative method: a research team member with a Ph.D. in Psychology will perform semi-structured interviews to obtain insight into participants’ perspectives on the intervention’s feasibility, acceptability, and usefulness and identify barriers and facilitators that may influence people with PD to participate in the program. This researcher is a skilled interviewer with no prior relationship with the participants. Two team members will transcribe verbatim the audio-recorded interviews into textual data using Microsoft Word. These researchers will independently perform an inductive thematic analysis process as described by Braun et al. (49). The analysis will be supported by QDA Miner Lite software. This process will allow the identification of themes emerging from the interview data through pre-analysis, encoding, categorization, and interpretation of the data.

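### With T1 tied to finishing the program, no final assessment described for people who stop, and a missed-sessions exclusion, the pre-post estimates are in effect completer-only

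*Protocol article*

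**What the plan says.** All of this is in the protocol article.

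- **Timing (Data collection).** For the secondary outcomes: "These assessments will be performed in the week before (T0) and after completing the training program (T1". No other final assessment is described. For people who withdraw, the record described is the reason.
- **Exclusion list (Sampling and recruitment).** Among the baseline exclusions stands an event that can only happen after enrollment: "Missed two consecutive sessions".
- **Analysis (Data analysis).** Change is tested in pairs: "the parametric two-tailed paired samples t-test will be employed if the normality assumptions are met". Otherwise the Wilcoxon signed-rank test is used. Both need T0 and T1 from the same person.
- **Retention, a primary feasibility domain (Data collection).** "Retention (percentage of enrolled participants who completed final program assessments".
- **Sample size (Sampling and recruitment).** "Both tests indicated a required sample size of 15 participants", and then "To account for a possible dropout rate of 25%, we increased the sample size to 20 participants".
- **Purpose (Data collection).** The secondary outcomes are to help choose the outcome of the later randomized trial and supply parameters for its sample size.
- **Discussion.** The authors accept that practicing safe landing may intimidate some people who fear falling.

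**The concern.** No single sentence limits the change scores to completers, but three provisions together do. T1 follows completion, anyone who misses two sessions running is excluded, and the tests use only people with both assessments. A participant who stops with at least two of the 16 sessions left meets the exclusion, has no described T1 and drops out of the comparison.

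Two things are at stake.

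1. **Selection related to the outcome.** The program aims to reduce fear of falling, and the Discussion names a route by which fear could make someone leave. If those who leave improve less, or get worse, the mean change in Short FES-I among completers is too favorable, and any fear made worse by the training goes unseen. The later trial would be planned on that figure.
2. **Retention loses its meaning.** If only completers reach T1, the retention percentage counts leaving the training and being lost to follow-up as one thing. A randomized trial analyzed by intention to treat needs to know whether people who stop training can still be assessed. The feasibility domains do not list program completion as a separate figure.

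**Working it through.** **Step 1. Reproduce the plan's figure.** Inputs from Sampling and recruitment: "taking into account a large effect size (dz = 0.8), an alpha level (α) of 0.05, and a statistical power (1-β) of 0.8", for the "two-tailed matched pairs t-test and the two-tailed matched pairs Wilcoxon signed-rank test".

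- Paired t-test, exact noncentral t: power is 0.790 at n = 14 and 0.821 at n = 15, so 15 pairs.
- Wilcoxon, with asymptotic relative efficiency 3/π (normal differences): power is 0.801 at n = 15, so 15 pairs.
- Dropout: 15 / (1 − 0.25) = 20.

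Both figures reproduce. The sample size is not in dispute.

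**Step 2. Who supplies a pair under the text as written.**

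| Participant | Missed-sessions exclusion | T1 described? | In the paired test? |
|---|---|---|---|
| Attends throughout, or misses scattered sessions | not met | yes | yes |
| Misses only the last session | not met | yes | yes |
| Stops with two or more sessions left | met | no | no |

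**Step 3. How far the estimate could move (illustration).** Assumptions, not in the documents: completers have mean change 0.8 and SD 1 (the planned dz), and a share q stops, with mean change m and SD s. Over all starters:

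- mean = (1 − q) × 0.8 + q × m
- variance = (1 − q) × 1 + q × s² + q(1 − q)(0.8 − m)²
- dz = mean / √variance

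With q = 0.25 (the plan's dropout allowance) and m = 0, the mean is 0.75 × 0.8 = 0.60, and the between-group term is 0.75 × 0.25 × 0.64 = 0.12.

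- s = 1: variance = 0.75 + 0.25 + 0.12 = 1.12; dz = 0.60 / 1.058 = 0.567.
- s = 0.5: variance = 0.75 + 0.0625 + 0.12 = 0.9325; dz = 0.60 / 0.966 = 0.621.

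Range over other assumptions, with s = 1:

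| Share who stop | m = +0.4 | m = 0 | m = −0.4 |
|---|---|---|---|
| 10% | 0.75 | 0.70 | 0.64 |
| 25% | 0.69 | 0.57 | 0.44 |

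For scale, a paired t-test at 80% power and two-sided 0.05 needs 15 pairs at dz = 0.8, 23 at 0.621 and 27 at 0.567. This compares paired tests. It is not the size of the later two-arm trial.

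**Step 4. How often the exclusion could apply (illustration).** Eight weeks at two sessions a week is 16 sessions. If sessions are missed independently with probability p, the chance of at least one run of two misses is 3.5% (p = 0.05), 13% (0.10), 26% (0.15) or 41% (0.20). At about 15% missed sessions, this rule alone could use up the 25% allowance.

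**The case against.** The strongest reply is that the T1 sentence does not withhold assessment from anyone. The week can be read as governing both the time before and the time after, and a fixed eight-week group course ends on one date for the whole group. On that reading T1 is already a calendar point. This stands: the sentence alone does not establish a completer-only design, and nothing forbids assessing people who stopped. It does not remove the exclusion or the paired tests, and the double reading means that staff could apply the sentence either way.

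A reader might go further than the documents allow in four ways.

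- **That raising 15 to 20 shows an intent to write off five people.** It does not. Such inflation is routine and would be done with a calendar-fixed T1 too.
- **That all pre-post estimates are affected.** Falls come from a weekly registry, data collected before withdrawal may be used, and people who miss scattered sessions still reach T1. The point covers Short FES-I, MDS-UPDRS, TUG and 6MWD.
- **That the missed-sessions rule is a side issue.** It is the firmer textual basis. Without it the point would rest on an ambiguous phrase.
- **That 15 against 27 is an error in the trial's planning.** It is an illustration for a paired test under assumed values.

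It is also fair that retention is worded as a follow-up measure, so it mixes the two kinds of loss only if people who stop are not assessed. The article also disclaims effectiveness and acknowledges the missing control group. Handling of missing T1 values may sit in a fuller document, but an analysis plan cannot recover a visit that was never sought.

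**Conclusion.** The concern holds in a limited form. Taken together, the T1 wording, the missed-sessions exclusion and the paired tests make the change estimates for the four scales and tests in effect completer-only. They also leave retention unable to separate stopping the program from loss to follow-up. This matters because the estimates are meant to inform the randomized trial, and the article itself gives a reason why stopping may be related to fear of falling.

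The size is unknown. If 25% stop with mean change 0 and completers have dz = 0.8, dz in all starters is about 0.57 to 0.62. With fewer people stopping, or some gain among them, the gap is smaller (0.75 at 10% stopping and a gain of 0.4 SD). If they worsen, it is larger (0.44 at 25% and a worsening of 0.4 SD). If they change as much as completers do, the mean change is not biased.

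**What to change.** - In Data collection, define T1 as the week after the group's eighth program week for everyone who started, whatever their attendance.
- In Sampling and recruitment, state that missing two consecutive sessions does not remove a person from assessment or analysis. Whether that person may go on attending sessions is a separate matter for the sponsor.
- Report two percentages: those who completed the program, and starters with a T1 assessment.
- In Data analysis, make the pre-post estimate in all starters with T1 the main one, and label the completer estimate as supportive.

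**Cost.** Changes of wording, and up to about five visits (25% of 20) within the planned enrollment. The sample size stays at 20. The pre-post change will probably look smaller. Some who stop will decline T1, so the selection is reduced and not removed, but the second percentage will show how much remains.
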